### Economic evaluation

An economic evaluation will be conducted alongside the trial to assess the cost-effectiveness of CBT compared to care as usual in the current study population. Information on costs and health outcomes will be prospectively collected during 24 months (starting at baseline until 18 months after birth) for both mother and child. Two complementary economic analyses will be conducted. The primary outcome measure of the planned cost-effectiveness analysis is the total emotional and behavioural problems score of the child according to the CBCL at 18 months of age.

In the additionally planned cost-utility analysis, QALYs (Quality Adjusted Life Years) will be used as the primary outcome measure. The study will be performed from a societal perspective. Medical costs that will be assessed include costs related to CBT, contacts with healthcare professionals, and medication use. Outside the healthcare sector, costs of informal care and productivity losses will be taken into account. Unit prices will largely be based on Dutch standard prices in order to facilitate comparisons with other economic evaluations. Cost-effectiveness acceptability curves will be used to inform decision-makers on the probability that the studied intervention is cost-effective.

This study protocol was approved by the medical ethical committee of the University Medical Centre Groningen.

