### Setting & Design

The source population will consist of all pregnant women in the Netherlands in the first trimester of their pregnancy. Women are recruited in obstetric care. In addition, we will invite pregnant women through advertisements in regional and national media targeted at pregnant women.

Women will be screened on anxiety and depression symptoms. Women with at least moderate symptoms of anxiety and/or depression at the end of the first trimester of pregnancy are either randomized to the intervention group in which they receive 10-14 sessions of CBT, or to the control group in which they receive care as usual.

Figure 1 shows the exact design of the study.

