### Study outcome measures

The primary outcome in this project is the total emotional and behavioural problems score of the child according to the Child Behaviour Check List 1.5 - 5 (CBCL 1.5-5) at 18 months of age.

Secondary outcomes are the child's mental and psychomotor development at 18 months of age, the change in depressive and anxious symptoms in the mother, obstetric variables such as birth weight, gestational age and Apgar score, the socio-demographic and lifestyle factors, such as alcohol use, smoking and education, and cost-effectiveness of the therapy.

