### Assessments

Women will be asked to fill in questionnaires until their child is 1.5 years. This will be done at 8 occasions: the screener at baseline (T0), the additional baseline information (T1), and follow-up questionnaires at 24 and 36 weeks of gestation (T3 and T4), at 6 weeks postpartum (T5), 6 months postpartum (T6), 12 months postpartum (T7) and 18 months postpartum (T8).

At all time points, levels of anxiety and depression are monitored by the 6-item State Trait Anxiety Inventory (STAI) and the Edinburgh Postnatal Depression Scale (EPDS). As to be found in table 1, all other questionnaires can be filled in once or at several time points.

**Table 1 T1:** Assessments per measurement

	T0	T1	T2	T3	T4	T5	T6	T7
**Depression (EPDS)**	X	X	X	X	X	X	X	X

**Anxiety (STAI)**	X	X	X	X	X	X	X	X

**Personality NEO-FFI**		X		X		X		

**Life events before pregnancy (NLEQ)**		X						

**Life events during pregnancy**		X		X		X		

**Perceived social support (SSQ)**		X						

**Coping styles (UCL)**		X	X	X	X			

**Attitudes (DAS)**		X	X	X	X			

**Maternal attachment (ECR)**		X					X	

**Quality of life (EQ-5D)**		X	X	X	X	X	X	

**Sociodemographic & -economic factors**		X						

**Lifestyle**		X		X		X		

**Breastfeeding**						X		

**General health**		X						

**Health care consumption**		X			X	X	X	

**Previous pregnancies**		X						

**Suicidality (MINI)**		X						

**Clinical Diagnostic Interview (SCID-II)**		X						

**Child Behaviour (CBCL)**								X

**Child development (BSID-II)**								X

For anxiety, we use the Dutch version of the 6-item STAI. This self report questionnaire is as valid as the full 20-item version and has frequently been used to measure antenatal anxiety [29]. For the screening on depression we use the EPDS, which has 10 items [31]. This is the most frequently used self report depression screener in the postnatal period as well as during pregnancy and has been found particularly valid during pregnancy because this scale omits somatic symptoms [30].

The following information will be obtained from participants. The exact time of administration can be found in table 1.

• Life events before pregnancy will be assessed at baseline, using the Negative Life Events Questionnaire [NLEQ, [32]].

• Perceived social support will be measured according to the 9-item Social Support Questionnaire (SSQ)-short form [33].

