• General health, socioeconomic position, ethnicity, smoking behavior, alcohol use, psychiatric history (whether the participant has had depression and/or anxiety symptoms before, whether she was treated for this and whether she is presently in treatment for these symptoms) will be assessed. Socioeconomic position will be assessed using five indicators: family income, educational level (father and mother), and occupational level (father and mother). This questionnaire is based on a questionnaire used in the Utrecht Health Project (Dutch acronym LRGP: Leidsche Rijn Gezondheids Project, http://www.zorggegevens.nl/zorg/eerstelijnszorg/leidsche-rijn-gezondheidsproject/). General health status will also be taken into account according to the EQ-5D [34].

• Personality will be assessed using the NEO Five Factor Inventory (NEO-FFI). The NEO-FFI is a shortened version of the NEO-PR-I [35] and covers the Big Five of personality (neuroticism, extraversion, openness, altruism and conscientiousness). These aspects each contain 6 subscales. The NEO-FFI contains 60 questions, 2 on each subscale. The present study will add 4 full subscales to the short version; two subscales of neuroticism, one of extraversion and one of conscientiousness. This is because we expect them to have the strongest association with persistence of depression and/or anxiety. The NEO-FFI is translated and validated in Dutch [36].

• Information on previous pregnancies, family size and composition, pregnancy related life events and on reactions on becoming a parent will be administered using questionnaires from the ALSPACstudy (http://www.bristol.ac.uk/alspac).

• Suicide risk will be measured using six screening questions from the MINI International Neuropsychiatric Interview [MINI, [37]].

• Maternal attachment style will be measured according to the ECR [38], which has been translated and validated for the Netherlands by Conradi et al. [39].

• Health care consumption will be assessed based on the TIC-P [40]. This instrument allows reliable recall over the past 6 months [41].

• Coping style will be assessed using the Utrechtse Coping Lijst, the UCL [42].

• A Dutch version of the Dysfunctional Attitude Scale (DAS) will be used to measure cognitions and attitudes [43].

• Obstetric variables such as gestational age, birth weight, Apgar score, complications such as (pre)eclampsia or HELLP, which will be obtained from midwifes. Women will be asked to give consent for this.

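### The economic evaluation is stated to run to 18 months after birth, but Table 1 last schedules EQ-5D and health care consumption at 12 months postpartum

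*Protocol article*

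**What the plan says.** The Economic evaluation section states that cost and health-outcome information "will be prospectively collected during 24 months (starting at baseline until 18 months after birth) for both mother and child". It plans two analyses from a societal perspective: a cost-effectiveness analysis on the child's CBCL total score at 18 months, and a cost-utility analysis on QALYs.

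The Assessments section leaves the timing of individual questionnaires to Table 1, which has eight columns, T0 to T7:
- The row beginning "Quality of life (EQ-5D" is marked at T1, T2, T3, T4, T5 and T6.
- The row "Health care consumption" is marked at T1, T4, T5 and T6.
- CBCL and BSID-II are marked at T7 only.

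On the cost questionnaire, the same section says: "This instrument allows reliable recall over the past 6 months".

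The running text of that section numbers the visits differently from the table. It omits T2 and ends its list with "6 months postpartum (T6), 12 months postpartum (T7) and 18 months postpartum (T8".

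**The concern.** The two places cannot both be right. One promises cost and health-outcome data up to 18 months after birth; the other, the only schedule in the article for the two instruments that supply them, stops 6 months earlier.

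What is at stake differs between the two analyses. For cost-effectiveness, the effect is collected at 18 months and only the cost side stops short, so numerator and denominator would cover different periods. For cost-utility, both costs and utilities are missing for the final 6 months. Any difference between arms in health care use, informal care, productivity or quality of life in that period would go unseen. The gap has to be settled before follow-up, because an analysis plan cannot recover data that were never collected.

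**Working it through.** **Step 1: which visit is each table column?** The text says "This will be done at 8 occasions", and the table has eight columns, so T0 to T7 are the eight visits in order: T0 screener, T1 baseline, T2 24 weeks, T3 36 weeks, T4 6 weeks postpartum, T5 6 months, T6 12 months, T7 18 months. Two independent anchors confirm the last two:
- Study outcome measures places the primary outcome, "Child Behaviour Check List 1.5 - 5 (CBCL 1.5-5) at 18 months of age", and Table 1 marks the CBCL at T7 only. So T7 is 18 months.
- Table 1 marks maternal attachment (ECR) at T1 and T6, and Data analysis compares attachment at month 12 with baseline as covariate. So T6 is 12 months.

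The last column is filled for EPDS, STAI, CBCL and BSID-II. The blanks for EQ-5D and health care consumption are therefore empty cells in a column that exists.

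**Step 2: reproduce the stated 24 months.** Setting & Design puts inclusion at the end of the first trimester ("at least moderate symptoms of anxiety and/or depression at the end of the first trimester of pregnancy") without giving a week. I assume baseline at week b and birth at week 40, with 365.25/12/7 = 4.348 weeks per month.

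Horizon in months = (40 − b)/4.348 + 18
- b = 12: 28/4.348 + 18 = 24.4
- b = 13: 27/4.348 + 18 = 24.2
- b = 14: 26/4.348 + 18 = 24.0
- b = 16: 24/4.348 + 18 = 23.5

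The stated 24 months is reproduced.

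**Step 3: the part with no measurement.** The last EQ-5D and the last cost questionnaire are at 12 months postpartum, which leaves 18 − 12 = 6 months.
- b = 12: 6/24.4 = 0.246
- b = 14: 6/24.0 = 0.25
- b = 16: 6/23.5 = 0.255

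The share is about 25% and hardly depends on the assumed baseline week.

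**Step 4: does anything else supply these data?** A 6-month recall looks backwards, so the 12-month questionnaire cannot cover months 12 to 18. The Randomisation section promises a record of care, but for the CAU arm only. No other section schedules EQ-5D or the cost questionnaire at 18 months.

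**Step 5 (conditional): recall during pregnancy.** After T1 the next cost questionnaire is T4, at 6 weeks postpartum. With 26-week recall and birth at week 40:

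Uncovered weeks = (40 − b + 6) − 26 = 20 − b
- b = 12: 8 weeks
- b = 14: 6 weeks
- b = 16: 4 weeks

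Birth at week 37 takes off 3 more, giving 5 weeks at b = 12 and 1 week at b = 16. For comparison, the step from 6 weeks to 6 months postpartum is 6 − 6/4.348 = 4.6 months, and from 6 to 12 months it is 6 months. Both fit the recall window.

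**The case against.** The strongest reply is that the intention is clear and the table may simply lack two crosses. The visit labels already disagree between text and table, and the diagnostic interview is called SCID-I in one place and SCID-II in another, so a clerical slip is as plausible as a schedule that really ends at 12 months. That stands: the document shows a contradiction, and it does not show which side is meant. It still has to be resolved, because sites working from the table would not collect the data.

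It can also be said that cost-effectiveness is a secondary outcome and that the primary comparison is untouched. That stands too, and it limits the weight of the point.

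A reader might go further in four ways that the document does not support:
- *That the economic results cannot be computed at all.* Costs and utilities are scheduled to 12 months and the CBCL at 18 months. Results to 18 months would need extrapolation, or the horizon could be shortened.
- *That half the horizon is missing*, by reading the table with the text's labels (T6 as 6 months: 12/24.2 = 0.50 at b = 13). This would put the CBCL at 12 months and the second attachment measure at 6 months, against the sections cited in the working. The same reading would put table T4 at 36 weeks' gestation, 23 weeks after a week-13 baseline, so the pregnancy recall gap would disappear.
- *That a fixed share near 31% of the cost period is unobserved*, by adding the pregnancy gap: (26 + 7)/(27 + 78) = 33/105 at b = 13. The 7 weeks rest on an unstated baseline week and on birth at term. The recall statement also concerns reliability; it does not say that care further back is wholly unobserved.
- *That the cost of CBT itself is lost.* The Economic evaluation section lists CBT costs separately from contacts with professionals, and nothing makes them depend on maternal recall.

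The record of care in the CAU arm has no stated end, so it is not true that nothing at all is recorded after 12 months. Being kept in one arm only, it cannot support a comparison.

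**Conclusion.** The contradiction between the Economic evaluation section and Table 1 is real and follows from the article alone. As scheduled, 6 months, about 25% of the stated horizon, have no cost or utility measurement comparable between arms. The 6-month figure rests on T6 being 12 months and T7 being 18 months, which the CBCL and attachment timings fix. The percentage also assumes baseline at 12 to 16 weeks and birth at 40 weeks.

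The recall gap in pregnancy is a secondary, conditional point: about 8 to 4 weeks over the same baseline range, and less with earlier birth.

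The issue is of moderate weight. It concerns a named secondary outcome and leaves the primary CBCL analysis and the sample size unchanged.

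**What to change.** - Mark EQ-5D and health care consumption at the 18-month visit in Table 1. The interval from 12 to 18 months equals the 6-month recall window, so this closes the main gap. Alternatively, restate the economic horizon as 12 months postpartum and explain how costs to 12 months relate to the 18-month CBCL effect.
- Use one set of visit labels in the text and in Table 1.
- Preferably, mark health care consumption at the 36-week visit as well. From a baseline at week 12 to 16 this is a recall of 24 to 20 weeks, and from week 36 to 6 weeks postpartum it is 10 weeks with birth at week 40, so consecutive windows then meet.

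Both visits already exist, and the Additional baseline data section says that all follow-up questionnaires are available online. The cost is a few minutes of extra respondent burden and a correction to the schedule. No visit is added.

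### The economic evaluation runs to 18 months after birth, but Table 1 stops the EQ-5D and the health care consumption form at 12 months, so about a quarter of the window has no utility or cost data

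*Protocol article*

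**What the plan says.** The Economic evaluation section fixes the period for costs and health outcomes as "prospectively collected during 24 months (starting at baseline until 18 months after birth) for both mother and child". It plans two analyses. The cost-effectiveness analysis takes the CBCL total problems score at 18 months as its effect. For the other, "In the additionally planned cost-utility analysis, QALYs (Quality Adjusted Life Years) will be used as the primary outcome measure". The costs to be counted are CBT, professional contacts and medication, plus informal care and lost productivity.

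Table 1 (Assessments) gives the collection schedule. The EQ-5D row has marks at T1, T2, T3, T4, T5 and T6. The row "Health care consumption" has marks at T1, T4, T5 and T6. Neither has a mark at T7, the last column. The consumption form is based on the TIC-P, of which the article says: "This instrument allows reliable recall over the past 6 months".

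Text and table number the visits differently. Both have eight occasions, but the text uses T0, T1 and T3 to T8, ending with "6 months postpartum (T6), 12 months postpartum (T7) and 18 months postpartum (T8"), while the table uses T0 to T7.

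**The concern.** The period promised for the economic data is longer than the period in which the two economic instruments are scheduled. Which visit carries a questionnaire is a data-collection decision, and no later analysis plan can recover answers that were never requested.

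If staff follow Table 1, the cost and QALY totals to 18 months cannot be computed from observed data. The analysts would have to shorten the horizon or extrapolate its last part. The cost-effectiveness ratio would have an effect measured at 18 months in one term and costs ending at 12 months in the other. The CBT rationale in the article rests on possible long-term protection, so the missing stretch bears on the question the economic evaluation is meant to answer.

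**Working it through.** **1. Which column is which visit.** Taking the eight occasions in order:

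| Text label | Table 1 column | Time |
|---|---|---|
| T0 | T0 | screener |
| T1 | T1 | baseline |
| T3 | T2 | 24 weeks of gestation |
| T4 | T3 | 36 weeks of gestation |
| T5 | T4 | 6 weeks postpartum |
| T6 | T5 | 6 months postpartum |
| T7 | T6 | 12 months postpartum |
| T8 | T7 | 18 months postpartum |

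Two independent anchors confirm the mapping. The CBCL and BSID-II are marked only in column T7, and Study outcome measures places the primary outcome as "Child Behaviour Check List 1.5 - 5 (CBCL 1.5-5) at 18 months of age". Attachment (ECR) is marked in columns T1 and T6, and Data analysis compares it at month 12 with baseline as covariate. So column T7 is 18 months and column T6 is 12 months.

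**2. Reproducing the stated 24 months.** Assumptions: baseline at week b = 12, 13 or 14 (the article gives only the end of the first trimester), birth at 40 weeks, 4.348 weeks per month.

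Window = (40 − b)/4.348 + 18

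- b = 12: 6.44 + 18 = 24.44 months
- b = 13: 6.21 + 18 = 24.21 months
- b = 14: 5.98 + 18 = 23.98 months

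This agrees with the article's 24.

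**3. The tail, for utilities and costs.** The last EQ-5D and the last consumption form fall at 12 months postpartum, which is 18.44, 18.21 or 17.98 months after baseline. The uncovered tail is 18 − 12 = 6.0 months, or 6.0/24.44 = 24.6% to 6.0/23.98 = 25.0% of the window.

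**4. The early gap, for costs only.** The T1 form looks back to before the window. The next one is at T4, 6 weeks postpartum (week 46).

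Time from baseline to T4 = (46 − b)/4.348 = 7.82, 7.59 or 7.36 months. Subtracting the 6-month recall leaves 1.82, 1.59 or 1.36 months of pregnancy uncovered.

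After T4 the recall periods join up: T4 to T5 is 6 − 6/4.348 = 4.62 months, and T5 to T6 is 6 months. Cost time covered = 6 + 4.62 + 6 = 16.62 months.

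Cost time uncovered = window − 16.62 = 7.82, 7.59 or 7.36 months, that is, the 6.0-month tail plus the 1.4 to 1.8 months in pregnancy.

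**5. After the change.** A form at column T7 with 6-month recall reaches back exactly to month 12, and an EQ-5D there extends the utility series to the full 24.0 to 24.4 months. A consumption form at column T3 (week 36) falls (36 − b)/4.348 = 5.52, 5.29 or 5.06 months after baseline, inside the 6-month recall, so it closes the early gap.

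**The case against.** The strongest reply is that this is a condensed article and Table 1 is not exhaustive. It has no row for the caregiver form, the language survey, the video observation or the obstetric data, all of which are planned in the text. The visit labels already contain slips, so two missing marks may be a reporting error, with the forms in fact scheduled at 18 months. That possibility stands, and it limits the claim: the documents show a contradiction, not that the data will certainly go uncollected. It does not remove the point. Both instruments do have rows, with explicit marks that stop at T6. The rows look intact: EPDS and STAI carry all eight marks, and CBCL and BSID-II line up at T7.

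No other source described in the article fills the gap. The record of care under Randomisation is promised for the control arm only and without a stated period, so it cannot give a between-arm contrast. CBT session records would supply intervention costs only. EPDS and STAI at 18 months are symptom scales, not the EQ-5D.

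It is also fair to say that the scope is limited. The 18-month CBCL itself is collected. The 4 to 8 postnatal CBT sessions are weekly, so unless they start very late the intervention costs fall before month 12.

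**Conclusion.** The Economic evaluation section and Table 1 contradict each other. Under Table 1, 6 of 24 months (about 25%) have no utility or cost data. The 25% rests only on the column mapping and the article's own 24 months. For costs, the total uncovered is about 7.4 to 7.8 months; that figure also rests on the stated 6-month recall and the assumed gestational weeks.

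Two stronger readings are not supported. A reader might apply the text's labels to the table, take T6 as 6 months postpartum and infer a 12-month gap (50%). The anchors rule this out, because the CBCL would then fall at 12 months. A reader might also infer a definite bias: with a constant utility difference d, 1.5d QALYs are seen instead of 2.0d, so cost per QALY is overstated by 2.0/1.5, about 33%. That needs a difference already present at baseline, no cost difference in months 12 to 18, and analysts who truncate. The documents give none of these, so neither the size nor the direction of any bias can be stated.

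The economic evaluation is secondary and the primary CBCL comparison is untouched. The point should be corrected because data missed at 18 months cannot be recovered.

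**What to change.** - Add the EQ-5D and the health care consumption form to the 18-month column (T7) of Table 1, so that the schedule matches the Economic evaluation section.
- Close the early cost gap: either add the consumption form at one pregnancy visit, for example column T3 (36 weeks), or have the T4 form ask back to baseline. The second option stretches recall beyond the 6 months for which the article claims reliability.
- Use one set of visit labels in text and table.
- Treat women who passed 18 months before the change as having missing data; do not shorten the horizon for everyone on their account.
- If the 18-month forms cannot be added, state that the cost and QALY horizon ends at 12 months postpartum, and that the CBCL-based ratio combines an 18-month effect with 12-month costs. This is second best: it makes the cost-utility analysis coherent but leaves the mismatch in the cost-effectiveness analysis.

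The cost is a small amendment and somewhat more questionnaire burden at visits that already take place. Women already complete the EPDS and STAI at 18 months, and the follow-up questionnaires are online.

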## Abbreviations

ADHD: Attention Deficit Hyperactivity Disorder; ALSPAC: Avon Longitudinal Study Parents And Children; BSID II: Bayley Scale of Infant Development; CAU: Care As Usual; CBCL: Child Behavioural CheckList; CBT: Cognitive Behavioural Therapy; C-TRF: Caregiver-Teacher Report Form; DALY: Daily Adjusted Life Years; DAS: Dysfunctional Attitudes Scale; DSM: Diagnostic and Statistical manual of Mental disorders; ECR: Experiences in Close Relationships scale; EPDS: Edinburgh Postnatal Depression Scale; EQ-5D: EuroQol; HELLP: Hemolytic anemia, Elevated Liver enzymes and Low Platelet count; ITT: Intention To Treat; LDS: Language Development Survey; MINI: Mini International Neuropsychiatric Interview; NEO-FFI: NEO Five Factor Inventory; NEO-PI-R: Revised NEO Personality Inventory; NLEQ: Negative Life Events Questionnaire; PROMISES: PRegnancy Outcomes after Maternity Intervention for Stressful EmotionS; QALY: Quality Adjusted Life Years; RCT: Randomised Controlled Trial; SCID: Structured Clinical Interview for DSM-VI Disorders; SSQ: Social Support Questionnaire; STAI: State and Trait Anxiety Inventory; TiC-P: Trimbos/iMTA questionnaire for Costs associated with Psychiatric illness; UCL: Utrechtse Coping Lijst.
